## Methods/Design

### Study Design

The study is designed as multicenter prospective randomised controlled trial in a three-factorial, split-plot plan (3x3xn) characterized as profile analysis (Figure 1) [38]. Thereby "aftercare treatment" appears as whole-plot factor with three categories respectively study arms (booklet, IRENA, RÜCKGEWINN) crossed with the sub-plot time factor that has also three categories (before and after rehabilitation and 12 month follow-up) [39]. The aftercare treatments will be carried out between 2^nd ^and 3^rd ^measurement. The third factor is the nested patient factor and is treated as random [40]. In addition, we stratify and control the trial for the covariables "chronicity staging", "gender", "rehabilitation facility" and "aftercare facility". Therefore, these covariables appear as additional factors.

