### Randomisation and Data management

In consideration of the logistic situation with several external and internal recruiting rehabilitation facilities and the provision of aftercare in diverse residential areas with miscellaneous aftercare patients in each aftercare facility, specific demands arise for the data management and the randomisation procedure. To accomplish a realisation with high scientific quality, we chose a largely electronic and internet-supported solution for data management including an online-randomisation feature. We implemented a data base for partly electronic data capturing where participants and patients not participating with the right inclusion diagnosis must be registered by the rehabilitation practitioners via a web-application. For an estimation of the participation ratio, all patients who meet one of the inclusion diagnoses are counted anonymously, independent of their participation in the study or any exclusion criterion. Registration of participants must be done before allocation is accomplished by the study software, so allocation concealment is assured automatically. For sequence generation we used an urn randomisation algorithm [66]. This algorithm is the most widely studied member of the family of adaptive biased-coin designs and provides a good compromise between controlling multivariate experimental bias and balancing the trial [67]. Advantages are good statistical properties, which force a small sized trial to be balanced and approaching complete randomisation as the sample size increases, with less vulnerability to allocation bias than permuted-block design. Consequently, an additional practical capability arises. The urn randomisation allows stratification for either large or small number of covariables with unknown prevalence. In this trial we stratify the randomization for "chronicity staging" with 3 subcategories, "gender" with two subcategories and "rehabilitation facility" with six participating centres.

Further purpose of the electronic data management system is that, as a planning tool and tool for data transfer and communication with corresponding facilities, it allows to support the organisation of the aftercare groups.

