### Statistical Hypotheses and Analysis

The primary question refers to the efficacy of the aftercare interventions in comparison to each other. This is related to treatment differences concerning the primary outcome (FFbH-R) during aftercare interventions and quantified by an interaction effect of the corresponding categories of the factors study arm and time between second and third general assessment. Furthermore, the additional single change over time in rehabilitation phases compared to the change effect of aftercare treatment and overall treatment efficacy of rehabilitation plus aftercare intervention should be evaluated for each aftercare treatment. In consideration of adjusting respectively maintaining the multiple α-error for the mentioned aims, multiple hypotheses will be tested in a closed test procedure [72]. Consistent with these objectives and the chosen factorial split-plot design with repeated measures, we use a saturated linear mixed effects model for statistical analysis and stratify for baseline and mentioned covariates [40,73]. To approach the linear change characteristics in two different phases (rehabilitation phases/aftercare treatment) as well as the total change, we use a structured additive linear mixed model with fractional polynomial b-splines with degree l = 1 (linear) and three knots κ_1 _- κ_3_, noted as follows [73]:

I: general form

Y=Uν+Xβ+Zγ+ε

II: reformuled

$$\begin{array}{l} y_{ij}=\beta_{0}+\gamma_{0i}+\beta_{1}t_{ij}+\beta_{2}t_{ij}I_{i}+\beta_{3}t_{ij}R_{i}+\gamma_{1i}t_{ij}+\nu_{1}T+\nu_{2}TI_{i}\\ \;\;+\nu_{3}TR_{i}+\beta_{4}AF_{i}+\beta_{5}RF_{i}+\beta_{6}MPSS_{i}+\beta_{7}G_{i}+\varepsilon_{ij} \end{array}$$

I_i _denotes the indicator variable for IRENA aftercare treatment and R_i _the indicator variable for RÜCKGEWINN aftercare treatment of individual i in a dummy coding with "booklet control" as reference category [73]. The corresponding *β_2 _*and *β_3 _*reflect directly the difference in "slope" of IRENA respectively RÜCKGEWINN to reference "booklet control" and for that reason the efficacy. AF an RF are dummy coded expressions for aftercare respectively rehabilitation facility of patient i, MPSS is also dummy coded variable for chronification stage according to Gerbershagen and G is a dichotomy gender variable. T denotes a suitable construction term for the b-spline for the additional effect (slope) of rehabilitation phases [73].

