At first hierarchical, global level in a closed test procedure a likelihood ratio test of the shown specified model against a zero model m_0 _is used with the following global linear hypotheses:

$$H_{0}:C_{AB}\beta =0\;\;H_{1}:C_{AB}\beta \neq 0$$

C is a suitable contrast matrix of fixed interaction effects:

$$C_{AB}=\left(\begin{array}{cccccccc} 0 & 0 & 1 & 0 & 0 & 0 & 0 & 0\\ 0 & 0 & 0 & 1 & 0 & 0 & 0 & 0\\ 0 & 0 & 1 & -1 & 0 & 0 & 0 & 0 \end{array}\right)$$

At second level of the test procedure, three single primary comparisons of change in functional capacity (FFbH-R) during aftercare treatments are performed with *β_i _*~*t(μ,σ^2^)*.:

$$\begin{array}{l} H_{0}:\beta_{2}=0\\ H_{0}:\beta_{3}=0\\ H_{0}:\beta_{2}-\beta_{3}=0 \end{array}\;\;\;\begin{array}{r} H_{1}:\beta_{2}\neq 0\\ H_{1}:\beta_{3}\neq 0\\ H_{1}:\beta_{2}-\beta_{3}\neq 0 \end{array}$$

As shown in the specified model, we consider the stratified analysis to be the primary analysis carried out with the corresponding intention to treat collective. Other analyses are conducted as sensitivity analyses.

To address secondary objectives of the study, the change of secondary outcomes in different aftercare treatments is also assessed. In order to identify effective components or partial goals that should be targeted in aftercare exercise programs, the time varying influence of secondary outcomes on the primary outcomes in the different treatments is modelled by multiple regression modelling.

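### The primary model adjusts FFbH-R levels, but not the aftercare slope it tests, for the three factors used to stratify randomisation

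*Protocol article*

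**What the plan says.** All references are to the protocol article.

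- **Randomisation and Data management**: "In this trial we stratify the randomization for 'chronicity staging' with 3 subcategories, 'gender' with two subcategories and 'rehabilitation facility' with six participating centres".
- **Study Design** gives a similar list for the trial as a whole: "we stratify and control the trial for the covariables 'chronicity staging', 'gender', 'rehabilitation facility' and 'aftercare facility". Aftercare facility is not among the randomisation factors and is left aside here.
- **Statistical Hypotheses and Analysis**, in words: "we use a saturated linear mixed effects model for statistical analysis and stratify for baseline and mentioned covariates".
- **Same section, the equation**: facility, chronicity stage and gender appear as β5 RF_i, β6 MPSS_i and β7 G_i. Each has a patient index and no product with t_ij or T. On their coding the article says "MPSS is also dummy coded variable for chronification stage according to Gerbershagen and G is a dichotomy gender variable".
- **Same section, the target**: efficacy is "quantified by an interaction effect of the corresponding categories of the factors study arm and time between second and third general assessment". The coefficients β2 and β3 "reflect directly the difference in 'slope' of IRENA respectively RÜCKGEWINN to reference 'booklet control' and for that reason the efficacy".
- **Same section, the status of the equation**: "As shown in the specified model, we consider the stratified analysis to be the primary analysis carried out with the corresponding intention to treat collective".

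**The concern.** The arms are deliberately balanced on three factors, and the analysis is described as stratified for them. The primary hypotheses concern change during aftercare. A term that is constant over time shifts a patient's level equally at all three assessments and says nothing about change. Any effect of chronicity stage, gender or facility on the course after dismissal is therefore left in the unexplained slope variation.

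Balanced allocation already removes that variation from the true sampling error of the arm comparison. A model that does not know this reports standard errors that are too large. Tests then run below the nominal 5%, intervals are too wide, and part of the precision bought by stratifying is lost. With only about 68 patients per arm expected in the analysis, that precision is worth keeping.

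This is not a detail awaiting an analysis plan, because the article prints the equation and names it as primary.

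**Working it through.** **1. The plan's own figure.** Inputs from Sample Size and Power Calculation: f = 0.27, α = 0.05, power 0.8, m = 8 fixed parameters. With N = 3 × 68 = 204, λ = f²N = 0.0729 × 204 = 14.87. A noncentral F test with m − 1 = 7 numerator degrees of freedom has power 0.800, so 68 per arm is reproduced. Then 68/0.6 = 113.3, rounded up to 114; 114/0.75 = 152; 152 × 3 = 456. None of these figures depends on the present point.

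**2. Algebra on the printed equation.** T carries the additional slope of the rehabilitation phase, so it is taken as constant between second and third assessment. The expected change is then

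E[y_i3 − y_i2] = (t_i3 − t_i2)(β1 + β2 I_i + β3 R_i).

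The terms in β5, β6 and β7 cancel exactly. The model gives every chronicity stage, gender and facility the same expected aftercare change within an arm.

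**3. What cancelling does to the estimate.** Generalised least-squares fits were run on simulated data with three arms, three visits and 68 per arm. Variances and covariate effects were assumed, since the article gives none.

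- Complete data, arm main effects added: estimates with and without the covariate main effects are identical.
- As printed (no arm main effects), t = 0 at baseline, intercept and slope uncorrelated, complete data: identical.
- As printed, t = 0 at baseline, intercept–slope covariance −40, complete data: the estimate shifts with SD about 0.24 points.
- As printed, t = 0 at dismissal, complete data: shift SD about 0.37 to 0.65 points.
- As printed, 40% missing at follow-up: shift SD about 0.14 to 0.72 points.

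So the covariates do not enter the modelled slope, but they can influence its estimate.

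**4. Standard error and type I error under balanced allocation.** Let R² be the share of variance in the second-to-third-assessment change that the three factors explain (assumed). If arms are perfectly balanced on them, the true SD of the contrast is √(1 − R²) times the standard error of a model that ignores them. Then:

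- type I error without slope adjustment = 2[1 − Φ(1.960/√(1 − R²))]
- power without slope adjustment = Φ(0.842/√(1 − R²))
- power with slope adjustment = Φ((1.960 + 0.842)/√(1 − R²) − 1.960)

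| R² | type I error, unadjusted | power, unadjusted | power, adjusted | difference (points) |
|---|---|---|---|---|
| 0.05 | 4.4% | 80.6% | 82.0% | 1.4 |
| 0.10 | 3.9% | 81.3% | 84.0% | 2.7 |
| 0.125 | 3.6% | 81.6% | 85.0% | 3.4 |
| 0.25 | 2.4% | 83.4% | 89.9% | 6.4 |

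A 5-point difference needs R² of about 0.19.

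**5. Simulation checks.**

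- The printed model for β3, with 204 complete cases, balanced allocation and 1,500 null trials per setting. At R² = 0.25 and t = 0 at baseline, the mean standard error was 2.98 against an empirical SD of 2.58, with type I error 2.4%. With covariate-by-time terms these became 2.57, 2.57 and 4.5%. With t = 0 at dismissal, the printed model gave 2.98, 2.66 and 2.9%; the extended model gave 2.57, 2.62 and 5.4%. At R² = 0.10, type I error was 3.3% and 4.3% as printed, and 4.3% and 5.9% extended. The Monte Carlo error of a 5% rate here is √(0.05 × 0.95/1500) = 0.56 points.
- The change contrast alone, with 204 patients and balanced allocation. At R² = 0.25 the standard error was 0.172 against a true SD of 0.153, with type I error 2.4% (4.8% with the strata). At R² = 0.10 it was 4.5% (5.3% with the strata). At R² = 0 including the strata cost essentially nothing.

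**The case against.** **Main effects do adjust the contrast.** A reader might infer from the cancelling terms that the covariates do nothing to the tested comparison. The documents do not support that. No arm main effects are printed, 40% drop-out is expected, and neither the origin of t nor the form of T is fixed. In simulations with t = 0 at dismissal, the main effects reduced the empirical SD from 2.65 to 2.54 (2.48 with covariate-by-time terms), or from 2.49 to 2.31 (2.27). This stands and limits the point to the slope. Those runs, however, drew the factors independently of arm. With allocation balanced on them, as the trial intends, the printed main effects left the standard error well above the true SD under both codings of t.

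**The power gain is easily exaggerated.** Comparing adjusted power with a flat 80% would suggest a gain of 10 points at R² = 0.25. That ignores that balance already helps the unadjusted estimate, so the proper difference is 6.4 points. Also, the plan's 80% belongs to a 7-degree-of-freedom F test, not to a pairwise contrast. With the same f and N, a 2-degree-of-freedom test has about 94% power and less to gain. Both objections stand. The power figures are for a hypothetical single contrast powered at 80%.

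**Main-effect adjustment is common, and the words may promise no more.** The stratified analysis is defined by reference to the equation, and the description as saturated may mean only the arm-by-time structure. That reading is possible. It removes the charge of outright contradiction, but not the mismatch between balancing on these factors and testing a change that the model does not adjust for them.

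**Everything depends on R².** Nothing in the article shows that the three factors predict change after dismissal. This stands.

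**Conclusion.** The point holds in a limited form. The primary model adjusts levels, not the aftercare slope, for rehabilitation facility, chronicity stage and gender. If these factors predict change after dismissal, the reported standard errors of β2, β3 and β2 − β3 are too large for the stratified allocation. The effect is small at modest R² and appreciable only near R² = 0.25.

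These sizes assume perfect balance, complete follow-up and an R² that the article does not supply. Urn randomisation and drop-out will make the real balance imperfect, which weakens the effect.

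A reader might infer a biased treatment effect or an inflated false-positive rate. Neither follows: allocation is randomised within these factors and the error is conservative. The sample-size figures are untouched. This is an inexpensive improvement that should be made, not a threat to validity.

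**What to change.** In the primary model of Statistical Hypotheses and Analysis, keep the main effects and add chronicity stage, gender and rehabilitation facility by t and by T. With complete follow-up, the equivalent is to model the change from second to third assessment with these three factors as covariates. Keep the contrasts β2, β3 and β2 − β3. The new terms cross the factors with time, not with arm, so the contrasts remain arm differences in slope and become adjusted for the strata. Extend the 8-column contrast matrix to match, and state the origin of t and the form of T. If only level adjustment is intended, the text should say so and stop calling the model saturated.

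Cost: no new data. The additions are 2 + 1 + 5 = 8 parameters per time term, 16 in all, against about 204 analysed patients. The count m = 8 in the sample-size section would no longer describe the analysis model and needs a remark. If the factors do not predict change, there is no gain and a few degrees of freedom are spent.

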### Ethical Aspects

The study sponsor being the Deutsche Rentenversicherung Bund (German Federal Pension Fund), which has an official assignment, this study inherently has to accomplish high ethical demands, especially in aspects of data privacy. Additionally, this investigation has been approved by the independent Research Ethics Committee of the Medical Faculty of Friedrich-Alexander-University of Erlangen-Nuremberg on 09.06.2009.

## Discussion

Chronic back pain comes along with a hardly mastered individual disease burden and intrusively affects all areas of life negatively. It has critical consequences on social and occupational participation and causes serious disability. Empirical evidence encourages the relevance of theories for the chronification process of back pain that demand mutually increasing physiological and psychosocial factors that surpass simple additive effect structures (e.g. fear-avoidance model). Thereby, it was shown that particularly by exercise-related and behaviour-related interventions, the appearance as well as the duration of future back pain episodes can be decreased [74-76]. Multidimensional concepts, which combine physical training with cognitive-behavioral components in a bio-psycho-social approach, are appreciated as especially promising [76]. Newer randomized controlled trials confirm these results [77-82]. Thus, we assume that the implementation of a specifically refined aftercare program with a high extent of therapy hours after a stationary rehabilitation leads to a stronger empowerment and a stronger development of self management competence than usual aftercare programs. In detail this should result in reduction of fear-avoidance beliefs as well as maladaptive coping strategies and, on the other side, in enhancement of self-efficacy, a stronger identification with and adherence to physical activity and, as a consequence, a reduction of deconditioning, and a sustainable encouragement of adaptive cognitive and behavioral coping strategies. Hence, we expect substantial and lasting improvements for the majority of the intervention group in view of pain-conditioned functional ability, pain intensity, pain-conditioned psychic disability as well as for subjective general quality of life. The beneficing of a back pain specific aftercare program therefore is obvious, and lies in the transference into the routine care and is also given by developed manuals with structured contents, media and material for organisation assistance as well as training draughts for therapists in aftercare.

Despite the possible high benefit for chronic back pain rehabilitants, special methodological and logistic challenges accrue in this study. A major logistic problem could possibly arise from low rate of patients that begin their prescribed aftercare. In usual aftercare this rate is about 18% concerning inpatient and about 43% concerning outpatient rehabilitation [83]. In this context we have to consider that once patients get back home from rehabilitation, the participation in an aftercare program collides with responsibilities of their daily life. In order to enhance the participation rate, we try to increase the liability of the aftercare for patients with a pre-registration in an aftercare facility when they are still in rehabilitation.
